## Background

With fierce social competition, accelerated pace of life, and the increasing mental stress, the incidence of insomnia is getting higher and higher. About 10 to 20% of people in the world suffer from insomnia, while the prevalence of insomniacs in adult is 33 to 50% [1, 2]. Long-term insomnia affects the neuroendocrine immune network system, resulting in multiple organ dysfunction and decreasing immune function and is often accompanied by anxiety and depression, daytime fatigue, cognitive dysfunction, and other injuries [3–5]. It can even cause traffic accidents, endanger personal and public safety, and place heavy burden on society and families [6–8]. Therefore, it is crucial for both individuals and the public to keep a healthy sleep without insomnia.

At present, there are many treatments for insomnia. Drug therapy is convenient, fast-acting, and still the most common treatment for insomnia [9]. However, a large number of studies have shown that long-term drug use is usually accompanied with adverse events, including ineffectiveness, drug resistance, forgetfulness, nightmare, and cognitive impairment [10]. Most insomniacs are eager to seek effective and safe treatments for insomnia. In the past two decades, non-pharmacological treatments have attracted increasing attention [11].

Acupuncture, as a natural therapy with a long history, has been widely used in Asian countries such as China and South Korea, because of its advantages of safety, effectiveness, and convenience [2]. According to a survey of private clinics, insomnia is one of the top ten acupuncture indications in the USA [12]. In recent years, more and more evidence has shown that acupuncture is safe and effective in treating insomnia [13–19]. Acupuncture is also included in Chinese guidelines for the diagnosis and treatment of insomnia [20]. However, as patients’ bad sleep behavior and wrong sleep cognition are not effectively corrected, the effect of acupuncture is usually short-term. In addition, most clinical studies seldom include long-term follow-up. Thus, the long-term effect of acupuncture on insomnia is still unclear.

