## Methods and design

### Study design

This study is a single-center, open label, randomized controlled trial and will be completed in the insomnia clinic of the Acupuncture and Rehabilitation Department of the Affiliated Hospital of Nanjing University of Chinese Medicine from 01 June 2020 to 30 December 2021. This study follows the principles of Consolidated Standards of Reporting Trials (CONSORT), [42] and Standards for Reporting Interventions in Clinical Trials of Acupuncture(STRICTA) [43] will recruit 90 subjects and randomly assign them to the acupuncture group, the TCM-eCBT-I group, and the acupuncture combined with the TCM-eCBT-I group, at a 1: 1: 1 ratio. Subjects will be interviewed before recruitment, by completing a structured insomnia diagnosis process (refer to the 2017 China Sleep Diagnostic [44] - Insomnia Diagnosis Process) to diagnose chronic insomnia, and they will be screened for other sleep disorders, mental disorders, and serious physical diseases and through formal medical history and sleep symptoms. All subjects also need to take PSQI assessment and record one week sleep diary in order to obtain baseline assessment data. Subsequently, 4 weeks of treatment and 24 weeks of follow-up will be conducted.

All subjects will complete the following scale evaluation: PSQI, ISI, and sleep diary to evaluate sleep; DBAS to evaluate sleep cognition and belief; HAMA and HAMD to evaluate mental state; and FS-14 to evaluate mental and physical fatigue. The above scales will be evaluated online in the insomnia TCM system during the 0th week, 4th week, 8th week, 16th week, and 28th week. Subjects will sign an informed consent form after evaluating the conformity for inclusion. The test process is shown in Fig. 1, and the time point of the assessment is shown in Fig. 2.

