### Statistical analysis

The statistics and analysis of all data will be conducted by an independent researcher who does not participate in the experiment. We will use the SPSS 22.0 statistical software for data analysis. Descriptive statistics will be used to describe the demographic data of sample groups, while the normality of the distribution of each parameter will be checked by histogram and the Kolmogorov-Smirnov test. A chi-squared test will be used to assess the sample characteristics and gender.

The measurement data were expressed as mean ± standard deviation (SD) or median (interquartile range) [M (IQR)]. The analysis of variance will be used to test the between-group differences for the PSQI, ISI, DBAS, HAMA, HAMD, FS-14 scores, and sleep diary. As to the comparisons of the three groups, normality and homogeneity of variance are analyzed by variance analysis. If the variance is not uniform or normality is not conformed, the Mann-Whitney *U*-test will be used. Counting data is chi-square test. All statistical tests will be conducted bilaterally, and *P* < 0.05 indicates statistical significance. Data analysis will follow the intention-to-treat principle including participants who are randomly assigned. Missing data will be input with the last observation carried forward method.

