## Discussion

The reason why insomnia is easy to become chronic is related to the patients’ bad beliefs and attitudes toward sleep, such as repeatedly worrying about the adverse consequences of insomnia and unrealistic expectations of sleep. These bad cognitions will lead to the patients’ nervousness and anxiety, leading to persistent over-awakening and aggravating insomnia. On the other hand, bad sleep habits, such as irregular sleep and excessive bedtime during the day, can also lead to circadian rhythm disorder, leading to and maintaining insomnia. CBT-I can improve insomnia by reducing poor cognition and control of sleep. It is suggested to be the first choice in treating insomnia [73]. However, due to the complicated process, long treatment cycle, high medical expenses, and the shortage of professional therapists in China, many insomniacs cannot benefit from it. In addition, domestic scholars have studied that after 4 weeks of eCBT-I treatment, only 57.9% of patients completed the treatment, suggesting that compliance for eCBT-I is low [54].

Acupuncture is effective, safe, and convenient, with high compliance of the patients in treating insomnia. However, because the patients’ bad sleep behavior and wrong sleep cognition have not been effectively corrected, the effect of acupuncture is only remarkable in the short term, but unstable in the long term. In addition, long-term acupuncture treatment is rarely carried out in most clinical studies, and the long-term effect of acupuncture on insomnia is unclear. Acupuncture and CBT-I have different key characteristics and behavioral requirements, which may be different in improving sleep, and each has its own advantages [74]. Combining the advantages of acupuncture and eCBT-I, this study actively corrects the unreasonable cognition of patients on sleep, develops good sleep hygiene habits, and achieves long-term and stable curative effects. Long-term follow-up will be conducted to provide clinicians with the best plan for insomniacs.

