## Trial status

This trial is recruiting patients now. Participant recruitment started on 20 October 2020 and is expected to end on 31 December 2021. This trial was registered in the Chinese Clinical Trial Registry on 17 May 2020. The registration number is ChiCTR2000032960. Protocol version 2, 31 March 2020.

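### Last observation carried forward as the only missing-data method assumes stable scores after loss, which the protocol itself does not expect, and can bias the week-28 comparison in either direction

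*Protocol article*

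**What the plan says.** The Statistical analysis section of the protocol article plans analysis of variance for PSQI and the other scores. It sets the analysis population with "Data analysis will follow the intention-to-treat principle including participants who are randomly assigned" and then gives a single rule for gaps: "Missing data will be input with the last observation carried forward method". No other method is named.

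The Study design section gives the timetable: "Subsequently, 4 weeks of treatment and 24 weeks of follow-up will be conducted", with scales completed "during the 0th week, 4th week, 8th week, 16th week, and 28th week". Week 4 is therefore the end of treatment, and weeks 8, 16 and 28 are follow-up.

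On the expected course after treatment, the Background states that "the effect of acupuncture is usually short-term". The Discussion repeats that the acupuncture benefit does not last reliably. It also cites guidelines that place a high risk of relapse in the six months after treatment stops, and gives this as the reason for the long follow-up. The Abstract presents the combination as a way to keep the benefit over time. The Sample size section allows 20% for loss and rejection.

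**The concern.** LOCF gives an unbiased arm mean at week 28 only if, on average, the scores of lost patients would not have changed after their last visit. The protocol's rationale says that they will change, and by different amounts in different arms: acupuncture alone is expected to fade, and the combination is meant to hold. Where the filled value is an end-of-treatment score, the relapse that follow-up is meant to detect is removed. Where it is a baseline score, the patient is counted as having had no change at all.

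The week-28 comparison between the combination and acupuncture alone is the one most exposed. The filled scores also enter the analysis of variance as if they had been observed, so the uncertainty of the imputation is ignored.

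**Working it through.** **The plan's own loss figure.** 72 / (1 − 0.20) = 90, so the stated inflation reproduces. It implies 90 × 0.20 = 18 patients lost, or 6 per arm if loss is equal. LOCF would then analyse 30 per arm as fully observed when 24 are.

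**Formula.** Let m0, m4 and m28 be an arm's mean PSQI at weeks 0, 4 and 28. Let e be the fraction lost before week 4 (baseline carried) and d the fraction lost between weeks 4 and 8 (week 4 carried). Assume that lost patients would have followed their arm's average course. Then:

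LOCF mean at week 28 = (1 − e − d) × m28 + d × m4 + e × m0.

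**Late loss only (e = 0).** The bias in one arm is d × (m4 − m28), that is, −d × relapse. With the same d in two arms, the bias in their difference has size d × (difference in relapse).
- Inputs: d = 0.20 (Sample size section); difference in relapse 1 to 3 PSQI points (assumed, not in the documents).
- 0.20 × 1 = 0.2 and 0.20 × 3 = 0.6 points.
- If relapse is the same in both arms, this bias is zero.
- If some of the 20% are lost after week 8 or week 16, only the relapse still to come is hidden. With steady relapse, 0.2 to 0.6 is then an upper range for equal loss at 20%.

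**Direction.** Assumed means: baseline 13; week 4 to week 28, acupuncture 7 to 10, TCM-eCBT-I 9 to 8, combined 6 to 6. The true week-28 differences are combined − acupuncture = −4.0 and combined − TCM-eCBT-I = −2.0.

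| Loss pattern | Acupuncture | TCM-eCBT-I | Combined | Combined − acupuncture | Combined − TCM-eCBT-I |
|---|---|---|---|---|---|
| 20% in each arm, after week 4 | 0.8×10 + 0.2×7 = 9.4 | 0.8×8 + 0.2×9 = 8.2 | 6.0 | −3.4 | −2.2 |
| 20% in each arm, before week 4 | 0.8×10 + 0.2×13 = 10.6 | 0.8×8 + 0.2×13 = 9.0 | 0.8×6 + 0.2×13 = 7.4 | −3.2 | −1.6 |

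Equal late loss shrinks one contrast and inflates the other.

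**No true difference at week 28.** Let both single-therapy arms have mean 9 at week 28, with week-4 means of 6 (acupuncture) and 9 (TCM-eCBT-I). With 20% late loss in each, LOCF gives 0.8×9 + 0.2×6 = 8.4 against 9.0. This is a false acupuncture advantage of 0.6 points. LOCF is therefore not reliably conservative.

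**The case against.** **Missing scores may be few.** The scales are completed online by the subjects (Data collection and management), and those who quit will be asked for a final evaluation (Privacy protection for participants). Stopping treatment is therefore not the same as having no later score. This reduces the problem but does not remove it, and the plan itself allows for 20% loss and rejection.

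**Bias in the comparison is not certain.** With equal loss and equal relapse it cancels. This stands: the documents give neither quantity by arm, so the right statement is that LOCF can bias the comparison. For early leavers, baseline may be close to the truth if they stopped treatment and gained little; the early-loss row above assumes that they would have done as well as the others.

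**The long-term comparison is not the only aim.** Short-term efficacy is an aim too, and no primary time point is named. At week 4, only loss before that visit matters. This limits the reach of the point, but week 28 remains exposed.

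**An analysis plan may add sensitivity analyses.** It may, so their absence here is no fault. The point is that the one method the article states is poorly suited to its own premise.

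Two stronger readings are tempting, and the documents support neither.
- The Discussion reports that "only 57.9% of patients completed the treatment, suggesting that compliance for eCBT-I is low". A reader might take 42.1% as the loss in the TCM-eCBT-I arms. The figure is completion of a 4-week treatment in another study. It does not measure missing assessments here and says nothing about loss after week 4. Multiplying it by 1 to 3 points of relapse (0.4 to 1.3) would pair eCBT-I attrition with the relapse expected after acupuncture. It would also imply about (42.1 + 42.1 + 20)/3 = 35% loss overall if acupuncture lost 20%, against the planned 20%.
- Study design places the trial "from 01 June 2020 to 30 December 2021", while Trial status says "Participant recruitment started on 20 October 2020 and is expected to end on 31 December 2021". A reader might infer that everyone enrolled after 10 June 2021 (30 December 2021 less 29 weeks) would have week 28 filled by LOCF. The dates do conflict, but Study setting and recruitment gives each subject 29 weeks, and nothing says that follow-up would be cut off. A wrong end date is at least as likely.

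**Conclusion.** The point holds. The article fixes LOCF as its only missing-data method, and LOCF's assumption contradicts the article's own account of what happens after week 4. The week-28 comparison can be wrong in either direction, and the precision will be overstated.

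The size is not known. The shift of 0.2 to 0.6 PSQI points rests on three assumptions: 20% loss in each arm, all of it between weeks 4 and 8; lost patients following their arm's average course; and a relapse difference of 1 to 3 points between arms. Only the 20% comes from the document, where it is an overall allowance that covers rejection as well as loss. No claim is made that loss will differ by arm, or by how much. The date conflict is a separate inconsistency and adds nothing to this size.

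**What to change.** Replace LOCF and the per-visit analysis of variance of PSQI with a likelihood-based mixed model for repeated measures:
- Outcome: PSQI at weeks 0, 4, 8, 16 and 28, with baseline in the outcome vector and not only as a covariate.
- Terms: arm, visit and arm-by-visit, with a common baseline mean and an unstructured covariance.
- Patients: every randomised patient with a baseline score contributes. A model with baseline only as a covariate would drop those with no later score, against the stated intention-to-treat aim.

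Multiple imputation over all visits is an acceptable alternative. Both assume that, given the observed scores and arm, loss does not depend on the unseen scores. So add one delta-adjusted or reference-based sensitivity analysis, and keep LOCF at most as a further sensitivity analysis.

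The cost is a paragraph of revised analysis wording and a little more analysis work. The scores are already scheduled, so no new data are needed.

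Separately, reconcile the study end date in Study design with the recruitment end in Trial status and the 29 weeks per subject. A subject who starts on 31 December 2021 would finish on 22 July 2022.

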### Data collection and management

Data will be collected and managed during the baseline period, before and after treatment, and during the follow-up period. Each assessment includes [1] a 20-min sleep-related online scale assessment in the insomnia Chinese medicine system, completed independently by subjects, and [2] a sleep diary prompted by the insomnia platform to subjects at 8:00 a.m.

### Privacy protection for participants

Only researchers and supervisors in this study may access the personal medical records of the subjects, and they will sign a “researcher statement” or “confidentiality commitment.” Data processing will use the method of “data anonymity,” omitting the information that can identify the personal identity of the subjects. If any subjects want to quit, the researchers will ask if they are willing to complete the final evaluation and record the last treatment time.

### Quality control

All researchers will receive special trainings; introduction of clinical consultation, acupuncture operation, and insomnia TCM system; and instructions on how to fill in the case report form. The acupuncturists hold a master’s degree in acupuncture and massage from the Nanjing University of Chinese Medicine. The assessors will receive professional training from psychologists. The data analysts will receive training in data input, coding, security, and storage. Statisticians will be trained in data evaluation and analysis. This study will be supervised by the Scientific Research Department of the Affiliated Hospital of Nanjing University of Chinese Medicine, so as to protect the rights and interests of subjects, to ensure the truthfulness, accuracy, and completeness of research data records and reports and to ensure that this study complies with the approved agreements and relevant regulations. The causes of loss will be recorded in detail by testing.

### Ethics and dissemination

This study is conducted in accordance with the Helsinki Declaration and has been approved by the Institutional Review Board of the Affiliated Hospital of Nanjing University of Chinese Medicine (2020 NL-018-02). All subjects and their families will be fully informed of the test situation and decide whether to participate in it. If the subjects agree to participate, they will be required to sign an informed consent. Any revision of this agreement will be reported and approved by the Institutional Review Board of the Affiliated Hospital of Nanjing University of Chinese Medicine. The results will be disseminated by publishing in an influential medical journal with an online version. We also plan to share the results with medical professionals, the public, and relevant organizations in the form of a conference report after it is published.

## Discussion

The reason why insomnia is easy to become chronic is related to the patients’ bad beliefs and attitudes toward sleep, such as repeatedly worrying about the adverse consequences of insomnia and unrealistic expectations of sleep. These bad cognitions will lead to the patients’ nervousness and anxiety, leading to persistent over-awakening and aggravating insomnia. On the other hand, bad sleep habits, such as irregular sleep and excessive bedtime during the day, can also lead to circadian rhythm disorder, leading to and maintaining insomnia. CBT-I can improve insomnia by reducing poor cognition and control of sleep. It is suggested to be the first choice in treating insomnia [73]. However, due to the complicated process, long treatment cycle, high medical expenses, and the shortage of professional therapists in China, many insomniacs cannot benefit from it. In addition, domestic scholars have studied that after 4 weeks of eCBT-I treatment, only 57.9% of patients completed the treatment, suggesting that compliance for eCBT-I is low [54].

Acupuncture is effective, safe, and convenient, with high compliance of the patients in treating insomnia. However, because the patients’ bad sleep behavior and wrong sleep cognition have not been effectively corrected, the effect of acupuncture is only remarkable in the short term, but unstable in the long term. In addition, long-term acupuncture treatment is rarely carried out in most clinical studies, and the long-term effect of acupuncture on insomnia is unclear. Acupuncture and CBT-I have different key characteristics and behavioral requirements, which may be different in improving sleep, and each has its own advantages [74]. Combining the advantages of acupuncture and eCBT-I, this study actively corrects the unreasonable cognition of patients on sleep, develops good sleep hygiene habits, and achieves long-term and stable curative effects. Long-term follow-up will be conducted to provide clinicians with the best plan for insomniacs.

A comparative study of acupuncture and CBT-I treatment of insomniacs with cancers shows that both treatments have shown good results in improving sleep through different mechanisms [75]. Previous studies have found that auricular acupuncture has a greater impact on sleep duration of insomniacs than CBT-I, [76, 77] while other studies have also shown that CBT-I was superior to acupuncture in treating insomnia, and showed similar improvements in fatigue, mood, and quality of life [78]. Due to the small number of studies, it is not yet possible to draw reliable conclusions.

In this study, the insomnia TCM system is integrated into the traditional exercises of Baduanjin exercise and five-element music to form TCM-eCBT-I, which are more suitable for Chinese people. Second, the effects of acupuncture, TCM-eCBT-I, and acupuncture combined with TCM-eCBT-I on the subjects’ subjective sleep, sleep attitude and belief, anxiety, depression, and daytime dysfunction will help doctors choose more appropriate treatments for insomniacs by evaluating the sleep-related scale and sleep diary. At the same time, the application of the insomnia TCM system provides a reference for exploring the chronic disease management mode of insomnia. According to the guidelines, the first 6 months after stopping treatment is a high-risk period for insomnia recurrence [79]. Therefore, long-term follow-up will be conducted through an online sleep diary and sleep scale score of the insomnia TCM system to observe its long-term curative effect. Of course, there are some localization and regrettable in the study. Recruitment of this study is limited to one center of Chinese First-class hospitals, and the sample size is too small so the results may not be applicable to other levels of hospitals or other countries. This study cannot blind subjects, which may lead to bias and affect the results. These limitations should be improved and supplemented in future studies.

## Trial status

This trial is recruiting patients now. Participant recruitment started on 20 October 2020 and is expected to end on 31 December 2021. This trial was registered in the Chinese Clinical Trial Registry on 17 May 2020. The registration number is ChiCTR2000032960. Protocol version 2, 31 March 2020.
